Studies examining the haemodynamic responses to blood flow restriction identify blood flow restriction aerobic exercise training as having lower haemodynamic stress than high intensity resistance training, while providing similar outcomes [38–40]. As such, blood flow restriction is purported to be a potentially beneficial addition to exercise for clinical populations who may be contraindicated to high-intensity resistance training. While blood flow restriction exercise is a novel addition to exercise among ESKD patients, pilot data from this laboratory (unpublished) indicates that haemodynamic responses (systolic blood pressure, diastolic blood pressure, mean arterial pressure, heart rate) do not differ markedly between low-intensity blood flow restriction and non-blood flow restriction aerobic exercise both performed during haemodialysis in this population.

Aerobic capacity and muscle strength are both key physiological factors underpinning physical function [41] and both can improve with blood flow restriction aerobic exercise training. As declines in physical function, muscle strength, and aerobic capacity, as well as accelerated muscle atrophy are common among patients with ESKD, blood flow restriction aerobic exercise training may present an opportunity to increase the efficiency of time spent exercising for this population.

This study will examine the efficacy of blood flow restriction aerobic training among patients with ESKD on haemodialysis (HD). We hypothesise that blood flow restriction aerobic exercise training will improve physical function, muscle strength, and muscle size among patients with ESKD beyond that of traditional aerobic exercise training.

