## Methods

### Design

This is a 12-week randomised controlled trial consisting of three groups randomised to exercise or usual care (Fig. 1). Participants will be randomised to one of three groups: a blood flow restriction cycling exercise training group (BFR-C), a non-blood flow restriction cycling exercise training group (CYC), or a non-exercising, usual care control group (CON).

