### Sample size calculation

The most relevant outcome for blood flow restriction training studies is knee extensor muscle strength, and this was used as the main primary outcome measure for calculating required sample size. Based on data from previous blood flow restriction research [25, 29, 32, 33], and previous exercise for ESKD research [18, 42, 43], the projected percentage changes in knee extensor muscle strength for each of the three groups are CON = −3%, CYC = 2%, BFR-C = 12%. The common standard deviation within group, based on the prior research was determined to be 15. Thus, to achieve a power of 80% at an α level of 0.05, 20 participants per group will be required to detect a difference between the expected means for percentage strength improvement. However, based on previous work conducted by this research group a conservative attrition rate of 20% is expected over 3 months due to voluntary patient withdrawal, death, additional hospitalisation, transfer to another facility, or patients receiving transplants [23]. Thus, a total of 75 participants will be recruited and randomly allocated to one of the three groups.

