### Statistical analysis

All statistical analyses will be performed using SPSS 22.0 (IBM Corp, Chicago IL, United States of America). Participant characteristic and demographic data will be presented using descriptive statistics, and compared using independent t-tests for continuous variables and chi-square tests for categorical variables. The distribution of data will be assessed for normality with a Shapiro-Wilks test (*P* > 0.05). Non-normally distributed data will be compared using the Friedman non-parametric test. Otherwise, comparisons between groups for all continuous primary and secondary variables measured will be made using one-way analysis of variance (ANOVA). Main effects will be analysed using a Tukey post hoc test. A significance level of *P* < 0.05 will be adopted for all statistical tests. All data will be presented as means ± SEM unless stated.

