## Discussion and conclusion

This study is the first to explore the efficacy of blood flow restriction aerobic exercise training among patients with ESKD. Additionally, it is one of the first to explore a battery of common clinical measures or physical function following a blood flow restriction aerobic exercise training program. The main objective of the study is to determine the effectiveness of blood flow restriction aerobic exercise training for improving the strength and physical function among patients with ESKD.

While exercise during dialysis is not a novel concept in the broader literature, the current exercise recommendations present a significant time and physical burden for patients with ESKD and does not have an established role in clinical practice. Therefore, this study is important given the well documented deficits in strength and physical function for patients with ESKD in conjunction with the rarity with which any exercise is adopted not only intradialytically, but in the broader ESKD population. It may also be valuable to include measures related to vascular stiffness (e.g. pulse wave velocity and vascular-related microRNAs), as this has also been shown to improve with exercise training, and may be enhanced with the addition of blood flow restriction [34, 70, 71].

It is expected that this study will provide an improved understanding of the role that blood flow restriction aerobic exercise training can play in providing an efficacious, time-efficient modality of intradialytic exercise for patients with ESKD, which caters to the population’s lower initial level of physical function and overall conditioning.

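### The hypothesis is BFR-C beyond CYC, but the analysis treats that contrast as one of three equal Tukey pairs, cutting its power to 39% for no needed error control

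*Protocol article*

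**What the plan says.** **Hypothesis (Background, last paragraph).** Restricted-flow training "will improve physical function, muscle strength, and muscle size among patients with ESKD beyond that of traditional aerobic exercise training". In terms of the arms, this is BFR-C against CYC.

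**Design.** "Participants will be randomised to one of three groups": BFR-C, CYC and usual care (CON).

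**Sample size calculation.** Of knee extensor strength the article says "this was used as the main primary outcome measure for calculating required sample size". The projected percentage changes are "CON = −3%, CYC = 2%, BFR-C = 12" per cent, with a common SD of 15. Twenty per group is said to give 80% power at α 0.05 "to detect a difference between the expected means for percentage strength improvement". No pair of arms is named.

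**Statistical analysis.** All continuous primary and secondary variables are compared across the three groups by one-way ANOVA, then: "Main effects will be analysed using a Tukey post hoc test". The level is 0.05 throughout. No pair is ranked above another, and nothing says which comparison tests the hypothesis.

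**Discussion and conclusion.** "The main objective of the study is to determine the effectiveness of blood flow restriction aerobic exercise training for improving the strength and physical function". No comparator is given.

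**The concern.** The hypothesis concerns one pair of arms, while the sample size and the analysis concern three arms jointly. Two things follow.

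First, the link from hypothesis to test is missing. A significant F, or a significant BFR-C versus CON result, is compatible with restriction adding nothing to cycling. Unless the plan says which contrast bears on the hypothesis, a reader cannot tell in advance which result would support it.

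Second, all-pairs Tukey shares the 5% error over BFR-C versus CON and CYC versus CON as well, and the hypothesis needs neither. The price is a stricter threshold for the contrast that matters, in a trial with only 20 evaluable participants per arm.

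**Working it through.** **Inputs.** All are from the Sample size calculation section: means −3 (CON), 2 (CYC) and 12 (BFR-C); SD 15; n = 20 evaluable per arm; α 0.05. The pooled error has 3 × (20 − 1) = 57 degrees of freedom. Sidedness is not stated; two-sided tests are assumed for pairs.

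**1. Reproduce the stated size.** The grand mean is 3.667 and the sum of squared deviations is 116.67. The noncentrality is λ = n × 116.67 / SD² = 20 × 116.67 / 225 = 10.37. The critical value is F(0.95; 2, 57) = 3.159. Noncentral F power is 80.9% at n = 20 and 78.6% at n = 19, so 20 per group is the smallest size for the omnibus F. With 20% attrition, 60 / 0.8 = 75. Both figures reproduce. A two-arm comparison does not give 20: by the normal approximation, 80% power needs 36 per arm for BFR-C versus CYC and 16 for BFR-C versus CON.

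**2. Threshold for one pair.** The standard error of a difference is 15 × √(2/20) = 4.743.
- Tukey: q(0.95; 3, 57)/√2 = 3.403/1.414 = 2.406, a per-pair two-sided level of 0.019. The observed difference must exceed about 2.406 × 4.743 = 11.4 points.
- Unadjusted, pooled error: t(0.975; 57) = 2.002. The observed difference must exceed about 9.5 points.

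The projected BFR-C minus CYC difference is 12 − 2 = 10 points. It lies between these thresholds.

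**3. Power by pair.** Noncentral t, 57 df, noncentrality = difference / 4.743:

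| Pair | Difference | Noncentrality | Tukey | Unadjusted 0.05 |
|---|---|---|---|---|
| BFR-C v CYC | 10 | 2.108 | 39.0% | 54.5% |
| BFR-C v CON | 15 | 3.162 | 77.3% | 87.5% |
| CYC v CON | 5 | 1.054 | 9.6% | 17.9% |

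**4. Joint behaviour.** Simulated trials (200,000, repeated with 400,000) under the protocol's means:
- omnibus F significant: 81%;
- F significant, Tukey BFR-C v CYC not: 42% of all trials, or 0.421 / 0.809 = 52% of those with a significant F;
- Tukey BFR-C v CON significant, BFR-C v CYC not: 41%.

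**5. Alternatives that hold 5%.**
- BFR-C v CYC alone, ungated, two-sided 0.05, pooled error: 54% power. The error for that contrast is 5% by construction.
- Unadjusted pairs only after a significant F: 53% power for BFR-C v CYC. For exactly three groups this is a closed procedure. If all arms are equal, any rejection requires a significant F (5%). If only one pair is equal, only one true null remains, and it is tested at 5%. In simulation the family-wise rate was 5.0% with all arms equal, and the rate for an equal BFR-C/CYC pair was 4.9–5.0% with CON different.

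Tukey therefore costs 53 − 39 = 14 percentage points against the second option, and 54.5 − 39.0 = 15.5 against the first.

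**6. What the change does not repair.** When F is significant, BFR-C v CYC still fails the unadjusted test in 28% of all trials (42% under Tukey). Reaching 80% on this contrast at two-sided 0.05 needs 36 to 37 evaluable per arm.

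**The case against.** **The contrast is already named.** The Background states one hypothesis, against traditional cycling. The Discussion sentence merely omits a comparator and contradicts nothing. This stands: a reader might infer that the article sets up several rival primary comparisons, and it does not. What is missing is the link from that hypothesis to the sample size and the analysis.

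**A false success claim would be misreporting, not a flaw in the plan.** This stands too. One might infer that the plan lets a significant F count as proof that restriction works. Nowhere does it say so, and Tukey shows BFR-C versus CYC separately, so a failure would be visible. A significant F when only CON differs is a correct rejection.

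**Tukey is a standard, valid method.** It is. It controls family-wise error over the pairs within an outcome and gives simultaneous confidence intervals, which protected pairwise testing does not. CYC versus CON also has some interest of its own. But validity is not the complaint. Tukey suits a design in which all pairs matter equally, whereas here one pair carries the hypothesis and equally safe procedures serve it better.

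**An unseen analysis plan may state the rule.** Possibly. But the article itself fixes the ANOVA, the post hoc method and an omnibus-based sample size, so the mismatch is in what it states.

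**Sample size, not Tukey, is the main driver.** Largely true; 54% is still low. That is why the fix must also touch the sample size text.

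**Conclusion.** The point holds as a cheap, worthwhile improvement, not as an error that invalidates the trial. The stated hypothesis rests on BFR-C versus CYC. The analysis tests it only as one of three equal pairs, at an effective two-sided level of about 0.019 and with 39% power, when 53–54% is available at the same 20 per arm with error still held at 5%.

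The stronger conclusions that type I error is inflated, or that the 20 per group is miscalculated, are not supported. Tukey controls error, and the sample size is correct for the omnibus F.

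The figures assume the protocol's projected means and SD, normal data with equal variances, exactly 20 evaluable per arm and two-sided pairwise tests.

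**What to change.** 1. **Statistical analysis.** Name BFR-C versus CYC on knee extensor strength as the contrast that tests the Background hypothesis. State that a significant F, or a significant BFR-C versus CON result alone, does not support that hypothesis.

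2. **Statistical analysis.** Choose one of these in place of Tukey for that outcome:
   - *Single contrast.* Test BFR-C versus CYC at two-sided 0.05 with the pooled ANOVA error, not gated by the F-test. Report the other two pairs as supportive.
   - *All three pairs confirmatory.* Use unadjusted pairwise tests only after a significant three-group F.

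3. **Sample size calculation.** State that the 80% refers to the omnibus F, and that power for BFR-C versus CYC at 20 per arm is about 53–54%, depending on the option chosen.

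**Cost.** Wording only; no extra participants, visits or data. Tukey's simultaneous intervals are lost, the other two pairs become supportive under the first option, and the stated power for the hypothesis will look less favourable than 80%.

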**Methods:**

This is a randomised controlled trial design. A total of 75 participants will be recruited from haemodialysis clinics. Participants will be allocated to a blood flow restriction cycling group, traditional cycling group or usual care control group. Both exercising groups will complete 3 months of cycling exercise, performed intradialytically, three times per week. The blood flow restriction cycling group will complete two 10-min cycling bouts separated by a 20-min rest at a subjective effort of 15 on a 6 to 20 rating scale. This will be done with pressurised cuffs fitted proximally on the active limbs during exercise at 50% of a pre-determined limb occlusion pressure. The traditional cycling group will perform a continuous 20-min bout of exercise at a subjective effort of 12 on the same subjective effort scale. These workloads and volumes are equivalent and allow for comparison of a common blood flow restriction aerobic exercise prescription and a traditional aerobic exercise prescription. The primary outcome measures are lower limb strength, assessed by a three repetition maximum leg extension test, as well as objective measures of physical function: six-minute walk test, 30-s sit to stand, and timed up and go. Secondary outcome measures include thigh muscle cross sectional area, body composition, routine pathology, quality of life, and physical activity engagement.

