#### Physical function

Objective physical function will be measured using the 30-s sit to stand test (STS30), the timed up and go test (TUG), and the six-minute walk test (6MWT).

The STS30 measures lower limb muscle strength and function and requires participants to stand from a chair and then return to the seated position as many times as possible in 30 s [59]. The test has also displayed strong comparative validity to lower extremity 1RM strength testing, particularly among community-dwelling older adults [59]. It has also demonstrated a high level of reliability among ESKD patients undergoing HD (ICC = 0.93) [60].

The TUG is a measure of dynamic balance and mobility requiring participants to stand from a chair, walk to and then around a cone placed 3 m away, walk back to the chair, and sit back down as quickly as possible. This test will be repeated three times, and an average time taken for accuracy purposes [61]. The TUG strongly reflects gait speed among older adults, and has shown strong test re-test reliability not only among older adults, but in ESKD patients undergoing HD (ICC = 0.91–0.96) [62–64].

The 6MWT is a self-paced assessment of aerobic capacity, and a strong index of all cause morbidity in older adults [65]. It requires participants to walk laps of a straight 30 m course with the objective to cover as much distance as possible in the six-minute duration [65]. The 6MWT is a reliable measure for patients with ESKD (ICC = 0.93–0.96) [60, 66]. It has also been validated against ⩒O_2_max for patients with ESKD, with moderate strength coefficients of correlation (*r* = 0.56–0.73) [11, 67].

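### Four primary outcomes are each tested at 0.05 with no order or adjustment, although the sample size ranks knee extensor strength first and spends the full 0.05 on it

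*Protocol article*

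**What the plan says.** The Methods part of the Abstract puts the primary outcomes in the plural: "The primary outcome measures are lower limb strength, assessed by a three repetition maximum leg extension test", together with "objective measures of physical function: six-minute walk test, 30-s sit to stand, and timed up and go". The section Primary outcome measures lists the same four under Lower-limb muscle strength and Physical function, and puts none above the others.

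The Sample size calculation does rank them. It calls knee extensor strength the most relevant outcome and says "this was used as the main primary outcome measure for calculating required sample size". Power of 80% at an α of 0.05 is computed for strength only.

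The Statistical analysis section does not repeat that ranking. It says that "comparisons between groups for all continuous primary and secondary variables measured will be made using one-way analysis of variance (ANOVA"), then that "Main effects will be analysed using a Tukey post hoc test", and sets P < "0.05 will be adopted for all statistical tests". It names no testing order, no split of α, and no rule on how many primary outcomes must succeed.

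**The concern.** The article has one leading primary outcome when the trial is sized and four equal ones when it is analysed. With four equal tests at 0.05, a reader who accepts any one significant result as a positive trial is no longer working at 5%. Tukey does not help here, because it protects the three arm pairs within one outcome and not the set of four outcomes.

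The headline claim, on strength and physical function, is at stake. The trial is also sized for only one of the four outcomes. If the four were kept equal and the error properly split, the planned number would no longer give the stated power for strength.

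**Working it through.** **Inputs.** From the Sample size calculation: expected changes "CON = −3%, CYC = 2%, BFR-C = 12" (in percent), common SD 15, α 0.05, power 80%, 20 per group, attrition 20%, total 75. From the Abstract and Primary outcome measures: four primary outcomes. From Statistical analysis: one-way ANOVA and Tukey for each outcome, P < 0.05 throughout. Correlations among the outcomes are not given, so they are assumed and varied.

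**1. Reproduce the plan's own sample size.**
- Mean of the three changes: (−3 + 2 + 12)/3 = 3.67.
- Squared deviations: 44.44 + 2.78 + 69.44 = 116.67.
- Cohen's f = √(116.67/3)/15 = 0.416.
- Noncentrality at 20 per group: 20 × 116.67/15² = 10.37.
- Power of the three-group F test (2 and 57 df, α 0.05): 80.9%. With 19 per group it is 78.6%, so 20 is the smallest number that reaches 80%.
- Attrition: 60/(1 − 0.20) = 75.

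The stated figures reproduce. The test behind them is the three-group omnibus test on strength alone, at the full 0.05.

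**2. Error rate across four outcomes, if any one success counts.** With independent outcomes, 1 − 0.95⁴ = 18.5%. For correlated outcomes, null trials were simulated: 40,000 per setting, three arms of 20, four equicorrelated normal outcomes.

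| Assumed correlation | ANOVA F | Tukey |
|---|---|---|
| 0 | 18.6% | 18.7% |
| 0.3 | 17.6% | 17.6% |
| 0.5 | 16.2% | 16.3% |
| 0.7 | 13.3% | 13.5% |
| 0.8 | 11.9% | 11.8% |
| 0.9 | 9.5% | 9.6% |

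Results with 25 per arm are nearly the same. The two columns agree within about 0.2 points, so using Tukey does not change the rate across outcomes. The secondary outcomes, also tested at 0.05, are not counted.

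**3. What four equal primaries would cost.** Bonferroni gives 0.05/4 = 0.0125 per outcome and an overall error of 1 − 0.9875⁴ = 4.9% if independent. At 0.0125, power for strength with 20 per group falls from 80.9% to 62.0%. Reaching 80% needs 28 per group (81.6%), which is 28/0.8 = 35 per group, or 105 in total after attrition.

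**4. Is BFR-C versus CYC already powered?** The difference is 12 − 2 = 10 and the SD is 15. At 20 per group, the noncentrality is 10/(15 × √(2/20)) = 2.11. A two-sided t-test at 0.05 then has 53.8% power, and the Tukey comparison (critical value 2.41 on 57 df) has 39.0%. By t-test, 80% power needs about 37 per group.

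**The case against.** **No any-one success rule is stated.** This is correct. The hypothesis in the Background covers function, strength and muscle size together, and the Discussion states the objective as strength and physical function. If all four outcomes had to succeed, the error rate would not be inflated. But the article does not state that rule either. The figures above are therefore conditional on how a positive trial is read.

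**Independence is unlikely.** This also stands. The article itself describes sit to stand as a measure of lower limb strength that compares well with 1RM testing. So 18.5% is an upper bound and not a likely value, and 13% is not a floor. Even at an assumed correlation of 0.9 the rate is about twice 5%.

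**A hierarchy already exists.** In part it does: strength is listed first and is called the main primary for sizing. But that wording serves the sample size only. The defect is that the ranking is not carried forward.

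**This is a condensed article, and a procedure across outcomes may sit in an analysis plan.** A common 0.05 threshold does not by itself exclude adjusted P values, since Tukey's P values are already adjusted and judged at 0.05. That softens the point. What remains is on the page: four primaries, one threshold for all tests, and a ranking used for sizing but not for analysis.

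**Conclusion.** The concern holds in a conditional form. The sizing of the trial and its analysis disagree on whether there is one leading primary outcome or four equal ones, and nothing in the article controls error across the four. If any single success would be read as a positive trial, the false positive risk under the global null is at most about 18.5%, and about 10% to 17.5% at assumed correlations from 0.9 down to 0.3, instead of 5%. This rests on normal outcomes, equal group sizes and assumed equal correlations.

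A reader might infer two stronger statements, and the article supports neither. The first is that the trial's error rate simply is 13% to 19%; that needs a success rule and correlations that the article does not give. The second is that the sample size already makes BFR-C versus CYC on strength the powered comparison. The 20 per group reproduces only as the three-group test, and that contrast has about 54% power by t-test or 39% by Tukey.

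**What to change.** Carry the ranking in the Sample size calculation into Primary outcome measures, the Abstract and Statistical analysis:

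- Name 3RM knee extensor strength as the single primary outcome. Test it with the three-group ANOVA at 0.05, followed by Tukey pairwise comparisons. This is the test that gives about 81% power at 20 per group.
- Make six-minute walk, 30-s sit to stand and timed up and go key secondary outcomes. Either test them with Holm adjustment only after strength is significant, or report them as estimates with 95% confidence intervals. Other schemes that control the error across outcomes would also serve.
- Do not describe BFR-C versus CYC as the contrast that the sample size powers. If it is to carry the main claim, it needs its own power calculation.

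The cost is wording in the outcome and analysis sections, with no change to the planned 75. The downside is that a function test alone can no longer carry the headline claim. The alternative, keeping four equal primaries with a Bonferroni split, would need about 105 participants to hold 80% power for strength.
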